### Sample size calculation and statistical considerations

Based on OS data with sorafenib from the SHARP study[6] and with yttrium-90 RE reported in the literature[9, 11–15], the number of patients required for randomisation to detect a clinically relevant increase (4 months) in OS time with RE versus sorafenib was determined as 400 patients (200 patients in each treatment arm). This translates to an expected median OS time of 10.7 months in the sorafenib group and 15 months in the RE group, with an accrual period of 24 months and follow-up of 12 months. These guarantee a power of 80% with a bilateral alpha risk of 5%. Estimating that up to 10% of patients that are recruited will not fulfil the criteria of eligibility for randomisation, we aimed to enrol 440 patients.

A Data Monitoring Committee (DMC) will regularly review the toxicity data to assess the safety profile of the treatment (including serious adverse events and mortality). The first intermediate analysis will take place once 30 patients have been followed up for at least 2 months in each treatment arm, after which the DMC will convene every 6 months.

### Statistical analysis

Results will be reported according to the Consolidated Standards of Reporting Trials (CONSORT) statement. An ITT analysis will be performed, keeping patients in their randomisation group and including protocol deviations. A ‘per-protocol’ sensitivity analysis will also be performed. A study flowchart will be provided, including the number of patients who: are eligible; are randomised to receive treatment; are followed up; withdraw from the study; and are lost to follow-up. Major protocol deviations and the reasons for withdrawal from the study will be described.

The Kaplan and Meier method will be used to calculate survival (OS and PFS). The comparison of survival rates at 12 months between the two treatment groups will be performed using the log rank test (Mantel-Haenszel version). In addition, the treatment effect, once adjusted for the stratified randomisation factors, will be calculated via: (1) a stratified log rank analysis; and (2) a Cox’s regression model.

The median survival times (OS and PFS) in both treatment groups will be calculated, along with the confidence interval associated with the difference or with the median survival time ratio[24].

Toxicity will be reported according to NCI CTCAE Version 3.0, with particular reference to the proportion of patients experiencing grade 3/4 toxicity in each treatment arm.

The objective response will be determined via the RECIST and modified (m)RECIST criteria, the EASL criteria for HCC, and the Choi criteria, and a comparison will be made between the two treatment groups using the ‘best response during follow-up’ criterion. The response rates will be calculated by comparing the number of patients who responded during follow-up (complete or partial response) with the total number of randomised patients in each group. The related confidence intervals will be calculated and compared between the two groups using Pearson’s chi-squared test.

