### Randomisation

Eligible patients will be randomised 1:1. The randomisation will be stratified by centre, Eastern Cooperative Oncology Group (ECOG) score (0 versus 1), the presence or absence of macroscopic vascular invasion seen on imaging (obstruction of the portal vein or its branches) and previous chemoembolisation failure. The list will be balanced by different sized blocks and randomly alternated. The data coordination centre will prepare the randomisation list before enrolment begins.

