### Outcome measures

The primary endpoint of the SARAH trial is OS. Secondary endpoints include: adverse events rate, progression-free survival (PFS) at 6 months according to RECIST[20], modified RECIST, EASL and Choi criteria; tumour response rate; general or liver disease-specific QoL scores; and cost of each strategy.

Cost endpoints are: the cost of RE from the hospital perspective; the average cost per patient from the payer’s perspective; and the incremental cost-effectiveness or cost-utility ratio.

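### The lead survival comparison is worded as 12-month rates tested by log-rank, which contradicts the OS definition, the follow-up plan and the basis of the 80% power

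*Protocol article*

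**What the plan says.** The protocol article's Outcome measures section states: "The primary endpoint of the SARAH trial is OS". Outcome definitions measures OS from randomisation to death from any cause and sets no time limit. Trial assessments has every patient other than the last one enrolled followed until that last patient's final visit, so most patients are observed for well over 12 months.

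The section Sample size calculation and statistical considerations assumes an "expected median OS time of 10.7 months in the sorafenib group and 15 months in the RE group". Recruitment is taken to last 24 months, and the study then runs for a further 12. On 400 patients, 200 per arm, the section concludes: "These guarantee a power of 80% with a bilateral alpha risk of 5" per cent.

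The Statistical analysis section first names Kaplan-Meier estimation for OS and PFS. Its next sentence, which specifies the Mantel-Haenszel form of the test, reads: "The comparison of survival rates at 12 months between the two treatment groups will be performed using the log rank test". The section adds a stratified log-rank analysis and a Cox model, both adjusting for the randomisation factors, and a confidence interval for the difference or ratio of median survival times. None of these additions mentions 12 months.

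**The concern.** The sentence joins two things that do not belong together. A survival rate at 12 months is a quantity at a fixed time. A log-rank test weighs the deaths in the two arms across the whole period of observation. An analyst following the sentence could do any of three things:

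- censor every patient at 12 months and run a log-rank test;
- compare the two 12-month survival proportions directly;
- treat the phrase as a slip and use all follow-up.

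These can give three different p-values for the primary endpoint. In an open-label trial that choice should not stay open while data accumulate. The first two options also leave out deaths that the stated power depends on.

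**Working it through.** **Inputs from the article.** Medians 10.7 and 15 months; 200 patients per arm, with allocation given as "Eligible patients will be randomised 1:1"; accrual 24 months plus 12 months' follow-up; two-sided alpha 5%; power 80%.

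**Assumptions not in the article.** Exponential survival, uniform accrual and no loss to follow-up. Observation time is then uniform between 12 and 36 months.

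**Step 1: hazards.** λ = ln 2 / median. This gives 0.0648 per month (sorafenib) and 0.0462 (RE). Hazard ratio = 10.7/15 = 0.713; ln HR = −0.338.

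**Step 2: reproduce the plan's figure.**
- Deaths required, Schoenfeld: 4(1.96 + 0.842)² / 0.338² ≈ 276. Freedman: (1.96 + 0.842)² × (1.713/0.287)² ≈ 281.
- Probability of death by the end of the study: 1 − [exp(−12λ) − exp(−36λ)] / (24λ) = 0.767 (sorafenib) and 0.653 (RE), mean 0.710.
- Patients required: 276/0.710 ≈ 389 or 281/0.710 ≈ 396, against 400 stated.
- Expected deaths with 400 patients: 200 × (0.767 + 0.653) ≈ 284.
- Power, Schoenfeld: Φ(½ × √284 × 0.338 − 1.96) = 81.2%. Freedman: 80.5%. A simulation of 10,000 trials gave 81.0%.

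The stated 80% is therefore reproduced by a log-rank test over all follow-up.

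**Step 3: log-rank test censored at 12 months.**
- Probability of death by 12 months: 1 − exp(−12λ) = 0.540 and 0.426.
- Deaths counted: 200 × (0.540 + 0.426) ≈ 193. Lost: 284 − 193 = 91, or 32%.
- Power: Φ(½ × √193 × 0.338 − 1.96) = 65.1% (Schoenfeld); 64.3% (Freedman); 65.1% by simulation.
- Patients needed to restore 80%: 276/0.483 ≈ 572 to 281/0.483 ≈ 582.

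**Step 4: direct comparison of 12-month survival.**
- Survival 46.0% and 57.4%; difference 0.115.
- Standard error: √[(0.460 × 0.540 + 0.574 × 0.426)/200] ≈ 0.050.
- Power about 63.7% with this unpooled error, 63.2% by the standard two-proportion formula and 63.9% by simulation.

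**Step 5: sensitivity.**

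| Setting | All follow-up | Log-rank censored at 12 months |
|---|---|---|
| 400 analysed, 10.7 vs 15 | 80.5–81.2% | 64.3–65.1% |
| 440 analysed, 10.7 vs 15 | 84.1–84.7% | 68.4–69.2% |
| 400 analysed, 10.7 vs 14.7 (the 4-month gain taken literally) | 75.8–76.5% | 59.3–60.1% |

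Trial assessments gives a maximum follow-up of 48 months, which does not match 24 + 12 = 36. If it implies 36 months of accrual, full follow-up yields about 308 deaths, and the share lost by stopping at 12 months rises to 37%.

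**The case against.** The strongest reply is that nobody intends to stop at 12 months. The article never says that data are censored there. OS has no horizon, earlier patients are followed to the end of the study, and the sample size reproduces only with full follow-up. The plan also calls for median OS in both arms. With 57.4% of the RE arm expected to be alive at 12 months, that median could not be estimated from data cut at that point. The phrase may be shorthand for an analysis made once the last patient has completed 12 months. The stratified log-rank and Cox analyses carry no limit.

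Most of this stands, and it makes loose drafting a credible explanation. It does not rescue the sentence. The shorthand reading cannot be confirmed from the text, and on any reading a log-rank test does not compare rates at 12 months. Nor is this a detail left to an analysis plan: the article states a rule, and states it wrongly.

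Some stronger readings are tempting but not supported:

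- **That the trial's power is 64–65%.** This follows only if the phrase is carried out.
- **That this is the only between-group survival test.** The stratified log-rank and Cox analyses follow it, and the article labels none of the tests as primary.
- **That data beyond 12 months exist for every survivor.** The last enrolled patient has only 12 months from the start of treatment. The death counts above allow for staggered entry.
- **That the sentence contradicts the secondary endpoint "progression-free survival (PFS) at 6 months according to RECIST".** PFS is named in the preceding Kaplan-Meier sentence. The comparison sentence says only survival rates, so extending it to PFS is inference.

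**Conclusion.** The sentence is wrong as written. It attaches a fixed-time quantity to a whole-curve test, and its 12-month limit contradicts the OS definition, the follow-up plan and the basis of the 80% power.

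The loss of power is conditional. With the limit applied, power falls by about 16 percentage points, from about 81% to about 64–65%, or to about 63–64% for a direct comparison of 12-month rates. Analysing all 440 patients would bring the truncated log-rank only to about 69%. If all follow-up is used, power is unaffected and the defect is one of wording. The figures rest on the assumptions listed with the calculation and on 400 patients analysed, except where 440 is stated.

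**What to change.** In the Statistical analysis section, delete *at 12 months* and reword the sentence, for example: OS will be compared between the arms by a two-sided log-rank test using all follow-up to the analysis cut-off; 12-month OS will be reported for each arm as a Kaplan-Meier estimate with a 95% confidence interval. The additional stratified log-rank and Cox analyses need no change on this point. Leave the status of the 6-month PFS endpoint as it is.

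The cost is one sentence, carried into the full protocol and analysis plan if they repeat the wording. No extra patients, visits or data are needed. The change should be made before any comparative survival data are examined.

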### Trial assessments

The last enrolled patient will be followed up for 12 months after the start of treatment (D0). All other patients will be followed up until the final visit of the last enrolled patient. Patients will therefore be followed up for a maximum of 48 months and a minimum of 12 months following start of treatment. All patients will be assessed by the schedule summarised in Table 2. Treatment will be discontinued if the patient withdraws consent, if the treating physician deems it necessary for medical reasons or if a serious adverse event occurs - after discontinuation, patients should be assessed by CT as soon as possible to assess response to treatment.

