In the SARAH trial, OS has been chosen as the primary endpoint as it is a more robust measure than PFS, and the SHARP trial demonstrated the efficacy of sorafenib based on this criterion. Moreover, the kinetics of tumour progression, as assessed from imaging techniques, is different between RE and sorafenib, rendering OS the best option for comparison between arms in this trial. An Asian study with similar inclusion criteria has now commenced, which compares sorafenib with RE in patients with locally advanced HCC[34], and could be used for meta-analysis in the future.

In addition to efficacy analyses, the SARAH trial offers the possibility of rigorously confirming the toxicity caused by sorafenib versus RE in patients with advanced HCC. This is important as the cardiovascular toxicity of sorafenib has been highlighted in a meta-analysis of cancer patients (predominantly renal carcinoma)[35], but was not a common complication in the SHARP study[6]. The SARAH trial will also offer the opportunity to conduct ancillary studies (for example, dosimetry and CT perfusion), and compare the cost of each treatment. A definitive economic evaluation of sorafenib therapy versus RE for advanced HCC is not currently available. It is therefore useful to: conduct a study using national data to establish the value of the resources used; take the specificities of local oncology practices into account; and compare sorafenib treatment to an up-to-date therapy, RE.

Limitations to the SARAH study design have been combated where feasible. While blinding is not possible due to the treatment methods, the potential biases caused by the lack of blinding have been minimised by the choice of OS as a robust primary endpoint. In addition, it is planned that an independent group of radiologists will perform a blind review of the imaging in order to guarantee the absence of bias regarding PFS.

The results from the SARAH trial should further the understanding of RE and determine the optimal treatment modality in advanced HCC. In addition, the data generated from this study may help to place RE into future consensus guidelines.

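### The emphasised grade 3/4 toxicity proportion ignores unequal time at risk; at equal constant toxicity it could show RE worse by about 3 to 7 points

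*Protocol article*

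**What the plan says.** All references are to the protocol article.

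- **Statistical analysis** reports toxicity by NCI CTCAE grade, "with particular reference to the proportion of patients experiencing grade 3/4 toxicity in each treatment arm". It names no counting window, time at risk or handling of death for this measure, and no test. Overall and progression-free survival, in the same section, get Kaplan-Meier and log-rank methods, with a Cox model for the adjusted treatment effect.
- **Table 2** records adverse events monthly from M1 to M9 and again at the end of participation.
- **Trial assessments** gives the last enrolled patient 12 months of follow-up, and "All other patients will be followed up until the final visit of the last enrolled patient".
- **Sample size calculation and statistical considerations** assumes an "expected median OS time of 10.7 months in the sorafenib group and 15 months in the RE group". Recruitment is taken to last 24 months, and a further 12 months of observation come after it.
- **Outcome measures** lists the adverse event rate as a secondary endpoint. The **Discussion** says that the trial offers the possibility of "rigorously confirming the toxicity caused by sorafenib versus RE".

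**The concern.** A grade 3/4 event can be counted only while the patient is alive and under observation. When events are collected to the end of participation, the time in which one can be recorded depends on survival, which is the primary endpoint. If the trial succeeds on its own assumptions, RE patients are observed for longer and have more opportunity to be counted. The crude proportion then mixes toxicity with survival. It leans against RE if RE prolongs life and in favour of RE if RE shortens it.

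Fewer side effects are part of the rationale in the Background, and the Discussion presents the safety comparison as a strength of the trial. The one measure given prominence is a weak basis for that comparison.

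**Working it through.** **Inputs from the article.** Median OS 10.7 v 15 months; accrual 24 months plus 12 months' follow-up; 200 patients per arm; 80% power; two-sided 5%.

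**Assumptions not in the article.** Exponential survival, uniform accrual, and a constant monthly hazard *h* of a first grade 3/4 event, taken as 0.02 to 0.10. The article gives no grade 3/4 rate and no expected difference between arms.

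**1. Reproduce the plan's sample size.**
- Death hazards λ = ln 2/10.7 = 0.0648 and ln 2/15 = 0.0462; hazard ratio 0.713, whose log is −0.338.
- Deaths needed (Schoenfeld): 4 × (1.960 + 0.842)² / 0.338² ≈ 276.
- Probability of death with follow-up uniform on 12 to 36 months: 1 − (e^(−12λ) − e^(−36λ))/(24λ) = 0.767 and 0.653, mean 0.710.
- N = 276/0.710 ≈ 389 (396 by Freedman's formula), close to the stated 400. The survival model therefore matches the plan's own.

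**2. Mean observed time** (probability of death divided by λ).
- Sorafenib: 0.767/0.0648 = 11.8 months.
- RE: 0.653/0.0462 = 14.1 months.
- Ratio 1.19.
- Trial assessments also states: "Patients will therefore be followed up for a maximum of 48 months and a minimum of 12 months following start of treatment". Since 24 + 12 is 36, a 48-month maximum was run as a sensitivity case (36 + 12). It gives 12.7 v 15.6 months, ratio 1.23.

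**3. Crude proportion at equal toxicity.** With k = h + λ:
- Full follow-up: p = (h/k) × [1 − (e^(−12k) − e^(−36k))/(24k)].
- Common window of W months: p = (h/k) × (1 − e^(−kW)).

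Example, h = 0.06, full follow-up. Sorafenib: k = 0.1248, p = 0.481 × 0.929 = 44.7%. RE: k = 0.1062, p = 0.565 × 0.899 = 50.8%. The excess is 6.1 points although toxicity is the same.

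RE minus sorafenib, in percentage points:

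| h per month | Full follow-up | 12 months | 9 months | 6 months | 3 months |
|---|---|---|---|---|---|
| 0.02 | 3.4 | 1.5 | 1.0 | 0.5 | 0.1 |
| 0.04 | 5.2 | 2.6 | 1.7 | 0.9 | 0.3 |
| 0.06 | 6.1 | 3.4 | 2.3 | 1.3 | 0.4 |
| 0.08 | 6.5 | 3.9 | 2.8 | 1.6 | 0.5 |
| 0.10 | 6.5 | 4.3 | 3.1 | 1.8 | 0.6 |

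With the 48-month maximum, the full follow-up column runs from 4.1 to 7.0.

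**4. How much of a true RE advantage survives.** The share kept is the crude difference with the planned survival divided by the crude difference if both arms had sorafenib survival. It was computed over full follow-up for a sorafenib proportion of 20% to 60%.

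| True toxicity rate ratio, RE/sorafenib | Share kept |
|---|---|
| 0.8 | 16% down to −8% (reversed) |
| 0.7 | 51% to 34% |
| 0.6 | 68% to 55% |
| 0.5 | 78% to 69% |
| 0.3 | 90% to 85% |

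**5. Check on the remedy.** Suppose identical toxicity occurs only in the first 3 months, with h = 0.10. The crude proportions are then nearly equal, at 23.7% v 24.3%. First events divided by event-free patient-months over full follow-up are 0.237/9.12 = 0.0260 on sorafenib and 0.243/10.82 = 0.0224 on RE. The ratio is 0.86, so RE would falsely look about 14% safer. For h from 0.05 to 0.20 the ratio is 0.86 to 0.87.

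**The case against.** **The wording is descriptive.** Toxicity is to be reported with emphasis on a proportion. Pearson's chi-squared test is named only for response rates, and nothing excludes a time-based summary, which an analysis plan not at hand may contain. This stands in part. A reader might go on to quote false-positive rates or lost power for a chi-squared test of toxicity, but the article names no such test. The point is limited to the measure that the article itself chose to emphasise.

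**A constant hazard fits these treatments poorly.** RE is given in one or a few sessions, while sorafenib is continuous with interruptions and dose reductions. Months alive are not the same as months at risk of treatment toxicity. This stands, and it is why the size is given by window. With early toxicity the distortion nearly disappears.

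**The proportion is a legitimate absolute risk.** By randomised arm, it is close to the cumulative incidence with death competing. This also stands, and it is a reason to keep the proportion. It does not make the proportion a comparison of toxicity when survival differs.

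**Two stronger readings are tempting.** One is that RE patients are at risk for 40% longer. That is the ratio of medians (15/10.7 = 1.40); with administrative censoring, observed time differs by 19% to 23%. The other is that a true RE advantage is roughly halved. That holds only for a toxicity rate ratio near 0.63 to 0.70 under a constant hazard, and the article gives neither.

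**Conclusion.** The point holds in limited form. The emphasised crude proportion takes no account of time at risk, which the plan's own survival assumptions make unequal. If toxicity accrues at an equal constant hazard of 0.02 to 0.10 per month, RE would look worse by about 3 to 7 points over full follow-up. The excess is about 1 to 3 points over 9 months, 0.5 to 2 over 6 months, and under 1 point over 3 months.

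The result rests on exponential survival at the planned medians, a survival difference actually occurring, and events continuing beyond the early months. If RE shortens survival, the distortion favours RE. How much of a true RE advantage would be masked cannot be stated, because it depends on an unknown rate ratio. This is a worthwhile, inexpensive improvement to the analysis wording. It does not mean that the planned proportion is wrong as a description.

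**What to change.** In Statistical analysis, keep the proportion with grade 3/4 toxicity per arm as a description and add:

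1. As the between-arm comparison, time to first grade 3/4 event, with a cause-specific Cox hazard ratio. Patients leave the risk set at death or last contact. State the time origin, because the article counts OS from randomisation and visits from D0, and the interval between the two differs by arm.
2. Rates by period, for example the first 3 months and later, because toxicity may be timed differently in the two arms.
3. Cumulative incidence of a first grade 3/4 event with death as a competing event.

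Do not rely on a single overall rate per patient-month. It errs in the other direction if toxicity is early.

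The cost is a few lines of analysis wording and one or two extra tables. Dates of events, death and last contact are needed, and routine adverse event recording normally supplies them. The small downside is that a hazard ratio is less familiar to readers than a percentage, so both should be shown. Visits, sample size and patient care are unaffected.

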**Table 2 Tab2:** **SARAH trial assessment schedule**

Visits	Enrolment/randomisation	D0	D15	M1	M2	M3	M4	M5	M6	M7	M8	M9	End of participation
Identification	X												
Verification of selection criteria	X												
Consent signature	X												
Initial assessment – history	X												
CT scan	X			X		X			X			X	X
CT perfusion	X			X		X			X				
Laboratory tests	X	X	X	X	X	X	X	X	X	X	X	X	X
Classification	X			X	X	X	X	X	X	X	X	X	X
Clinical examination				X	X	X	X	X	X	X	X	X	X
Quality of life questionnaires	X			X		X			X			X	X
Preparatory angiography		X											
Scintigraphy		X											
RE		X											
Start of sorafenib treatment		X											
Retreatment^*^				X	X	X	X	X	X	X	X	X	
Cancer progression monitoring				X	X	X	X	X	X	X	X	X	X
Sorafenib monitoring				X	X	X	X	X	X	X	X	X	X
Concomitant medication				X	X	X	X	X	X	X	X	X	X
Adverse events				X	X	X	X	X	X	X	X	X	X

^*^Timing of retreatment depends upon type of retreatment (see text). CT, computed tomography; D, day; M, month; RE, radioembolisation.

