In the RE arm, patients randomised to RE will require a hepatic angiogram, and a liver-to-lung shunt pre-assessment with technetium-99 m (^99m^Tc)-marked human serum albumin in order to determine their suitability for the RE procedure. Accessory tumoural vascular branches and extrahepatic vascular branches will be embolised using thrombogenic coils or vascular plugs in order to isolate the arterial supply of the afferent vessel that vascularises the tumour. A catheter will then be placed in the afferent vessel that vascularises the tumour, and 150 to 180 MBq of ^99m^Tc-marked human serum albumin will be injected. The injection rate and catheter position will mimic the anticipated RE procedure. After the injection, the patient will have the pulmonary shunt evaluated using a dual-head gamma camera or single-photon emission computed tomography (SPECT)/computed tomography (CT). The prescribed activity of SIR-Spheres™ will then be calculated based on the patient’s body surface area and the percentage tumour involvement as described by Kennedy *et al*.[19]. Patients who would receive a dose in the lungs higher than 25 Gy based on the liver-to-lung shunt pre-assessment will not receive RE, but will remain in this study arm as part of the intention-to-treat group (ITT). Patients who are eligible for RE will commence treatment between the second and fifth week after randomisation with a single session of treatment (the day on which RE is administered is defined as D0 in Table 2). In patients with bilobar involvement, contralateral RE will be administered within 30 to 60 days. In order to avoid premature retreatment with RE of any lobe due to late tumour response, retreatment with RE will only be considered beyond 3 months from D0 in the absence of objective response or if there is significant progression on imaging (stable or progressor according to the response evaluation criteria in solid tumours (RECIST) or European Association for the Study of the Liver (EASL)) in the treated region (same tumour or new tumour). Retreatment with RE will also be considered beyond 6 weeks in the event of partial failure of the initial treatment due to an identified correctible cause or if an insufficient tumour dose was delivered.

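### The response rate counts any response up to study close, so a response first seen after anticancer therapy outside the randomised strategy is credited to the randomised arm

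*Protocol article*

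**What the plan says.** Tumour response rate is one of several secondary endpoints (Outcome measures). The Statistical analysis section compares the arms on "best response during follow-up" and forms the rate by "comparing the number of patients who responded during follow-up (complete or partial response) with the total number of randomised patients in each group". The test is Pearson's chi-squared.

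Trial assessments defines follow-up. The last recruit is followed for 12 months, and for the rest "All other patients will be followed up until the final visit of the last enrolled patient". The result is given as "Patients will therefore be followed up for a maximum of 48 months and a minimum of 12 months following start of treatment". No exception is made for patients who have stopped treatment; the only related instruction is that "after discontinuation, patients should be assessed by CT as soon as possible to assess response to treatment".

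Table 2 schedules CT at enrolment, at months 1, 3, 6 and 9, and at the end of participation.

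The Treatments section allows further RE within the RE arm: contralateral treatment at 30 to 60 days for bilobar disease, and later "retreatment with RE will only be considered beyond 3 months from D0 in the absence of objective response or if there is significant progression". It also keeps in the RE arm, for the intention-to-treat analysis, patients who are not given RE because the predicted lung dose exceeds 25 Gy.

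**The concern.** The window for best response is the whole of follow-up, and follow-up does not end when the assigned treatment ends. A patient who stops sorafenib, starts a different anticancer therapy and then shows a partial response meets the definition of a sorafenib responder. A patient in the RE arm who never receives RE, is given something else and responds meets the definition of an RE responder.

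The response rate would then measure a mixture of the randomised strategy and whatever came after it. If later therapy differs between arms, which an open-label design makes possible, the chi-squared comparison can shift in either direction. The planned blinded imaging review (Discussion) does not protect against this, because a genuine response to a later therapy still reads as a response on the scan.

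**Working it through.** **Step 1. Does anything close the window?**

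| Element | Where | What it fixes |
|---|---|---|
| Numerator | Statistical analysis | Complete or partial response at any time in follow-up |
| Denominator | Statistical analysis | All randomised in the arm |
| End of follow-up | Trial assessments | Common closing date; 12 to 48 months from start of treatment |
| CT after stopping | Trial assessments | One prompt scan; not said to be the last that counts |
| Last scheduled CT | Table 2 | End of participation |

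Nothing in the article ends the response window at the end of assigned treatment, at progression or at the start of another therapy. The end-of-participation CT can fall long after the assigned treatment stopped.

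**Step 2. Can the size be derived?** No. The sample size section powers overall survival only. The article states no expected response rate for either arm and no frequency of later therapy. There is no planned figure for response to reproduce.

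**Step 3. Illustration on assumptions.** The 200 per arm and the two-sided 5% level are the sample size section's figures for overall survival. True response rates of 10% (sorafenib) and 20% (RE) are assumed. A fraction c of an arm's non-responders gains a late response that is credited to the arm:

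credited rate = p + (1 − p) × c

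The fraction c is the share of non-responders given another therapy times the response to it. With an assumed share of 10% to 30% and response of 20% to 40%, c runs from 0.10 × 0.20 = 2% to 0.30 × 0.40 = 12%. For an arm at 10%, that adds 0.90 × 0.02 = 1.8 to 0.90 × 0.12 = 10.8 points. The table uses c = 5% and 10%.

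Power = Φ{[|p1 − p2| − 1.96 × √(2p̄(1 − p̄)/n)] / √([p1(1 − p1) + p2(1 − p2)]/n)}, where p̄ is the mean of p1 and p2 and n = 200.

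Worked base case, 10% v 20%: p̄ = 0.15; null standard error √(2 × 0.15 × 0.85/200) = 0.0357; alternative standard error √((0.09 + 0.16)/200) = 0.0354; (0.10 − 1.96 × 0.0357)/0.0354 = 0.85; power 80.2%.

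| Late credit | Sorafenib | RE | Power |
|---|---|---|---|
| None | 10.0% | 20.0% | 80.2% |
| 5%, sorafenib arm only | 14.5% | 20.0% | 30.7% |
| 10%, sorafenib arm only | 19.0% | 20.0% | 4.4% |
| 5%, RE arm only | 10.0% | 24.0% | 96.4% |
| 10%, RE arm only | 10.0% | 28.0% | 99.7% |
| 5%, both arms | 14.5% | 24.0% | 67.5% |

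The higher powers are not a benefit. They come from a difference widened from 10 to 14 or 18 points by treatment outside the strategy.

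If both true rates are 10%, late credit to 5% of non-responders in one arm only (10.0% v 14.5%) gives a 27.8% chance of a significant result favouring that arm. Credit to 10% (10.0% v 19.0%) gives 72.6%. Equal credit in both arms leaves the chance at 2.5% in each direction.

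**The case against.** **A cut-off rule is normally left to the full protocol or the analysis plan.** This is true of the detail, and neither document is shown. But the article does not leave the window open for later definition. It names all of follow-up, twice, and defines follow-up elsewhere. A cut-off would change that stated rule.

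**Non-trial therapy is never mentioned.** This stands. The article neither permits nor forbids later anticancer therapy, and crossover is not described. A reader might infer that such responses will in fact be credited, or will differ by arm; the documents show only that they would count if they occurred.

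**RE retreatment is part of the assigned treatment.** This stands. A reader might infer that a response after retreatment is misattributed. The Treatments section makes retreatment part of the RE strategy, so counting the response under intention to treat is legitimate.

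**The window is less wide in practice than 48 months suggests.** This largely stands. That is the maximum, the minimum is 12 months, and after month 9 only the end-of-participation CT is scheduled. The expected median survivals are 10.7 and 15 months. These facts limit the effect without removing it.

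**A cut-off at first progression could itself bias the comparison.** This stands against using it as the main rule. The Treatments section anticipates late response to RE, contralateral RE can follow the month 1 CT, and the Discussion says that progression on imaging has different kinetics in the two arms. Some RE patients could be fixed as non-responders before their assigned treatment is complete.

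**The illustration is arbitrary.** This stands as to size. The only RE response figure in the article is 78 to 89% from earlier studies (Discussion), far from the assumed 20%.

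**Conclusion.** The point holds in a limited form. As written, a complete or partial response at any time up to the closing date counts for the randomised arm, including one first seen after anticancer therapy outside the randomised strategy. This can distort the response comparison.

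The documents do not support saying that it does distort it, in which direction or by how much. The powers in the working, from 4.4% to 99.7% around a base of 80.2%, rest wholly on assumed response rates, an assumed amount of late credit and an assumed arm in which it falls. Nor do the documents support treating responses to protocol RE retreatment as errors of attribution, or requiring that the main analysis stop at first progression.

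The consequence is confined to a secondary endpoint. The primary endpoint, overall survival, and its sample size are unaffected.

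**What to change.** In the main response analysis, take the best response from randomisation up to the start of any anticancer therapy outside the randomised strategy, and keep every randomised patient in the denominator. State that contralateral RE and protocol RE retreatment belong to the RE strategy and do not close the window. Report responses first seen after retreatment for progression on a separate line, so that readers can see how much of the RE rate depends on them.

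Give two sensitivity analyses: the any-time rate as now written, and a rate cut off at first progression by the same response criterion. Agreement among the three would show that the choice of window does not matter.

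The cost is a short definition, one cut-off date in the programming, and collection of the start dates of later anticancer therapies if they are not already recorded. Response rates may come out slightly lower. The change concerns analysis only and leaves patient management and the scan schedule as they are.
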